### Randomisation

The participants will be randomly assigned (1:1) to the intervention or control group after the baseline assessment. Randomisation will be done using a computer-generated programme, using random blocks of four sizes. A researcher who is not immediately engaged in the project will implement the randomisation process.

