### Primary outcome measures

The primary outcomes for the study are related with its feasibility and time to partial or complete recovery of each instrumental ADLs.

To evaluate the feasibility of this study, the following primary outcomes will be assessed:

Recruitment time frame: proportion of participants recruited within 7 days after onset of symptoms. It will be assessed by dividing the number of participants recruited within the time frame divided by the total number of participants.Beginning of the intervention: proportion of participants that started any of the interventions no later than 15 days after onset of symptoms.Adherence to each component of the intervention: proportion of adherence to each component of the intervention and different intervention modalities (remote/in person), calculated as the number of sessions attended divided by the total number of sessions provided. For the COGWEB training, the outcome will be the absolute number of sessions.Dropout: proportion of participants who dropped out of the study, calculated as the number of participants who dropped out after attending at least one session divided by the total number of participants who attended at least one session.

Time to recovery in each instrumental activity of daily living will be measured by an adapted version of the Frenchay Activities Index (FAI). The translated and validated version of the FAI—adapted version for the Portuguese population^23^ will be used to assess the instrumental ADLs functional performance at baseline and follow-up at 3 months. The version used in this study is based on the perception of the patient’s capacity to perform a specific instrumental ADLs instead of its frequency, as stated in the original scale developed by Holbrook and Skilbeck.^24^ The scale consists of 15 activities, scored from 1 to 4 (1-could not do at all; 2-very difficult; 3-a little difficult; 4-not difficult at all).^23^ Although the original index suggests that total scores for men and women should be considered separately,^24^ in the present study the score of each activity will be analysed independently, as the interest in exploring the impact of the programme in each activity.

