For the present study, only activities that are part of participants’ daily lives will be considered, namely those that were performed at least once in the last 12 months. Time to recovery will be defined as the time from the start of the intervention programme to the time of complete or partial recovery. Each participant will report their level of performance in each activity at the baseline and follow-up at 3 months. In the baseline, if a participant scores a specific activity as altered (score 1–3), their level of performance before the TIA or minor stroke will be confirmed to understand if the change in the activity performance is related with the cerebrovascular event. It will be also inquired and recorded the date when a difficulty in a certain activity ceased. The average of activities altered post-event (score 1, 2, 3) at baseline and the average of activities that improved in both groups on completing the intervention programme will be measured.

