### Data analysis and sample size

The associations between the social and clinical characteristics and feasibility (eg, recruitment time frame, adherence, dropouts) and lifestyle outcomes will be quantified through linear or logistic regression models, as applicable. Time in days from the onset of symptoms to complete or partial recovery in each instrumental ADLs will be estimated and illustrated by Kaplan-Meier survival curves. The time comparison between intervention and control groups will be made through the log-rank test. To estimate the association between the intervention and the recovery time, HRs will be estimated, through the computation of univariate and multivariate Cox regression models.

Training of the interviewers and use of standardised procedures for data collection is expected to contribute to a low proportion of missing data, and no imputation is being planned.

To the best of our knowledge, there is no previous information regarding effect sizes and SDs regarding the primary outcome related with the recovery of functionality after a TIA or a minor stroke. Nevertheless, a sample size of at least 70 participants (35 per arm) is commonly recommended for a pilot study when estimating the pooled SD.^25^ Nevertheless, taking into account the results of a previous RCT evaluating a cardiac model of rehabilitation for reducing risk factors post-TIA and stroke,^26^ this sample size will allow to detect mean differences of 5.5 and 6.0 in the changes observed in the Hospital Anxiety and Depression Scale—anxiety and depression scores, respectively, between intervention and control groups (assuming a statistical power of 80% and a level of significance of 5%).

To achieve the sample size needed to accomplish the proposed objectives, we expect to invite approximately 100 individuals, since a participation of 70% was previously observed in the EPIPorto cohort.^27^ We also expect a dropout of 10% from baseline to the first follow-up; nevertheless, and in order to minimise refusals and losses to follow-up, all activities will take place near participants’ residence and be scheduled for their convenience.

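### Time to recovery is compared by an unstratified log-rank test, which is valid but may be less efficient than one using the activity score already recorded before randomisation

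*Protocol article*

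**What the plan says.** All places are in the protocol article.

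- **Data analysis and sample size.** The event time is "Time in days from the onset of symptoms to complete or partial recovery in each instrumental ADLs", shown by Kaplan-Meier curves. The between-arm test is then fixed: "The time comparison between intervention and control groups will be made through the log-rank test". The following sentence adds that "HRs will be estimated, through the computation of univariate and multivariate Cox regression models". No covariates are named, and no Cox model is declared the main comparison.
- **Primary outcome measures.** Each of 15 activities is scored on four levels: "1-could not do at all; 2-very difficult; 3-a little difficult; 4-not difficult at all". Scores of 1 to 3 at baseline count as altered. The score is taken twice: "Each participant will report their level of performance in each activity at the baseline and follow-up at 3 months". Activities are analysed one by one.
- **Randomisation.** "The participants will be randomly assigned (1:1) to the intervention or control group after the baseline assessment". Blocks are used, and no stratification factor is described.
- **Study design.** The trial is a superiority pilot, meant among other things to sharpen the power and sample size calculation of a later full-scale trial.

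**The concern.** Participants enter the analysis of an activity at different starting points: unable to do it, finding it very difficult, or finding it a little difficult. This starting score is the baseline value of the outcome itself, so it is a natural candidate to predict when the difficulty ends. If it does predict recovery, pooling the three levels mixes different hazards. An unstratified log-rank test then has less power than one that compares arms within score, and the unadjusted hazard ratio is closer to 1 than the ratio at a given score.

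With at most 35 per arm, and fewer on any one activity, chance imbalance in starting severity can be appreciable. Neither the randomisation as described nor the stated test uses the score. The adjustment variable is measured before allocation, so using it needs no new data. At stake are the efficiency of the only between-arm test named for time to recovery, and clarity about which hazard ratio the pilot passes on to the full trial.

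**Working it through.** **The plan's own figures.** None is given for time to recovery: no power, effect size or event count. The only power statement concerns the anxiety and depression scores (differences of 5.5 and 6.0). It does not bear on this point and cannot be checked, because no SD is given.

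**Inputs from the document.** 70 participants allocated 1:1; expected dropout 10%, so 70 × 0.9 = 63 analysed; follow-up 3 months (90 days used); baseline scores 1 to 3. The 5% level is stated only for the anxiety and depression scores and is taken here as two-sided.

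**Assumptions not in the document.** Exponential recovery times, censoring at 90 days, treatment hazard ratio (HR) 2.0 at a given score, and a recovery hazard multiplied by k for each score point:

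hazard = base × HR^arm × k^(score − 2)

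Three set-ups were simulated:

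- **A:** equal shares of scores 1, 2 and 3; 70% control recovery; 3,000 trials per scenario.
- **B:** shares 20/30/50%; median recovery 45 days in controls at score 2; 2,500 trials.
- **C:** as A, but few altered participants, mostly at score 3 (shares 10/20/70% or 5/15/80%); 2,500 trials.

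The Monte Carlo standard error is at most √(0.5 × 0.5 / 2,500) = 1.0 point.

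**Check of the simulation.** In B with k = 1 and n = 70 there were 59.1 events on average. Schoenfeld's formula gives power = Φ(√(59.1/4) × ln 2 − 1.96) = Φ(0.704) = 76%. The simulated log-rank power was 76.6%.

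**Power (%)**

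| Set-up | n | k | Log-rank | Stratified log-rank | Cox with score | Cox minus log-rank |
|---|---|---|---|---|---|---|
| A | 63 | 1.5 | 64 | 66 | 68 | +4 |
| A | 63 | 2 | 54 | 64 | 68 | +14 |
| A | 63 | 3 | 39 | 62 | 65 | +26 |
| A | 40 | 2 | 38 | 43 | 48 | +10 |
| B | 70 | 1 | 76.6 | 73.2 | 74.9 | −1.7 |
| B | 70 | 1.5 | 69.9 | 72.9 | 75.5 | +5.6 |
| B | 70 | 2 | 59.5 | 71.2 | 73.1 | +13.6 |
| B | 70 | 3 | 46.2 | 71.5 | 74.0 | +27.8 |
| B | 30 | 1 | 41.1 | 35.8 | 39.5 | −1.6 |
| B | 30 | 2 | 31.6 | 36.4 | 40.0 | +8.4 |
| C 10/20/70 | 40 | 1.5 | 47.6 | – | 50.1 | +2.5 |
| C 10/20/70 | 40 | 2 | 41.5 | – | 46.6 | +5.1 |
| C 10/20/70 | 25 | 1.5 | 32.4 | – | 31.6 | −0.8 |
| C 10/20/70 | 25 | 2 | 28.7 | – | 31.9 | +3.2 |
| C 5/15/80 | 40 | 1.5 | 47.4 | – | 48.2 | +0.8 |
| C 5/15/80 | 40 | 2 | 44.2 | – | 47.6 | +3.4 |

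**Type I error** (HR 1.0) was about 5% for all three methods; in set-up B it ranged from 4.5% to 6.2%.

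**Unadjusted HR.** In large samples (n = 20,000, set-up B) it was 1.98, 1.91, 1.77 and 1.59 for k = 1, 1.5, 2 and 3. The adjusted HR stayed at about 2.0. In set-up C the unadjusted HR was 1.87 to 1.98.

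**Caution on the Cox column.** The fitted model used a linear score, which is how the data were generated, so this column is somewhat favourable. The stratified test makes no such assumption. Its gain over the plain log-rank test is 10 points (A: 64 − 54) to 11.7 (B: 71.2 − 59.5) at k = 2, and 23 (62 − 39) to 25.3 (71.5 − 46.2) at k = 3. With k = 1 it loses 3.4 points at n = 70 (76.6 − 73.2) and 5.3 at n = 30 (41.1 − 35.8).

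**The case against.** The strongest reply is that adjustment is already planned. The sentence after the log-rank test lists multivariate Cox models, and the choice of covariates is something an article may leave to a fuller document. This largely stands. A reader might infer that the plan ignores baseline severity altogether; the text does not support that. What remains is that the article does fix the between-arm comparison, and fixes it as the unstratified test.

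A reader might also infer that the log-rank test is wrong or that the unadjusted HR is biased. Neither follows. The type I error holds. The smaller unadjusted HR is a different estimand (the HR is non-collapsible), and it is the right planning input if the full trial is to use an unadjusted test. Nor does the document say that the unadjusted HR will feed the later sample size; it says only that the pilot will help that calculation.

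The size of the gain is also open to challenge. Eligibility (NIHSS up to 3, modified Rankin 0 to 2, discharged home) makes it plausible that few participants are altered on a given activity and that most of them score 3. In those runs the difference is about 0 to 5 points, with power around 50% or lower either way.

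Finally, the event is complete or partial recovery. Someone at score 1 has several steps available and someone at 3 has only one, so the hazard need not rise steadily with the score. This counts against a linear score term, but not against using the score.

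No power claim is contradicted, because the document makes none for time to recovery.

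**Conclusion.** The point holds as a matter of efficiency, not validity. The stated between-arm test leaves out a baseline value of the outcome that is measured before allocation, and the adjusted model that is listed is neither tied to that value nor made the main comparison.

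At an assumed HR of 2.0, adjustment changes power by about nil if the score is not prognostic or if few participants are altered and most score 3. The gain is about 14 points if the hazard doubles per score point with 63 to 70 analysed, and 26 to 28 points if it triples. The HR, the prognostic strength, the number altered per activity and the mix of scores are all assumptions; the document gives none of them. The trade still favours adjustment: a small, bounded cost against a gain that may be substantial.

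**What to change.** In Data analysis and sample size:

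1. State that the main between-arm comparison for each activity is the Cox model with arm and that activity's baseline score as a prespecified covariate, and that the HR and p-value come from it. Enter the score as categories or as strata, with a prespecified rule for collapsing sparse levels, rather than as a linear term.
2. Keep the Kaplan-Meier curves and the unadjusted log-rank test as descriptive or sensitivity analyses.
3. When planning the full trial, use the HR (marginal or conditional) that matches its intended analysis.

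The cost is wording only, since the score is already collected. The statistical downside is one or two extra parameters in activities with few events. If the score is not prognostic, the one-parameter adjustment cost about 1 to 2 power points in the simulations and stratification about 4. The version with three categories was not simulated.

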**Methods and analysis:**

Patients diagnosed with a TIA or a minor stroke are being recruited at the emergency or neurology departments of the Hospital Pedro Hispano, located in Matosinhos, Portugal (n=70). Those who accept to participate will be randomly allocated to two groups (1:1): (a) Intervention—receives a 3 months combined approach, initiating early post-event, composed of cognitive training, physical exercise, nutrition, psychoeducation and assessment/correction of hearing loss; (b) Control—participants will not be subject to any intervention. Both groups will receive the usual standard of care provided to these diseases. Recruitment began in May 2022 and is expected to continue until March 2023. Socio-demographic characteristics, lifestyles, health status, cognitive function, symptoms of anxiety and depression and quality of life will be assessed; as well as anthropometry, blood pressure and physical condition. Time to complete or partial recovery of instrumental activities of daily living will be assessed using an adapted version of the Frenchay Activities Index. All participants will be evaluated before the intervention and after 3 months.

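### The 80% power stated for the HADS changes assumes 70 participants assessed at 3 months; the plan's own 10% dropout leaves about 63 and power near 76%

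*Protocol article*

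**What the plan says.** All the figures come from the section on data analysis and sample size in the protocol article.

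- **Target.** The size rests on a pilot convention: "a sample size of at least 70 participants (35 per arm) is commonly recommended for a pilot study when estimating the pooled SD". The abstract attaches n=70 to the patients being recruited.
- **Power.** Drawing on an earlier trial of cardiac-style rehabilitation after TIA and stroke, the section says that "this sample size will allow to detect mean differences of 5.5 and 6.0 in the changes observed in the Hospital Anxiety and Depression Scale" anxiety and depression scores, at 80% power and 5% significance. It gives no SD and does not say whether the test is one- or two-sided.
- **Invitations.** "we expect to invite approximately 100 individuals, since a participation of 70% was previously observed in the EPIPorto cohort".
- **Dropout.** The next sentence reads "We also expect a dropout of 10% from baseline to the first follow-up". What follows it is a set of measures to limit losses (sessions close to home, convenient scheduling), not an adjusted number.
- **Missing data.** Interviewer training and standardised procedures "is expected to contribute to a low proportion of missing data, and no imputation is being planned".

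The section on secondary outcome measures places the HADS among the secondary outcomes, measured at baseline and at 3 months.

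**The concern.** The power sentence is about changes in HADS score. A participant without a 3-month score has no change, and without imputation does not enter that comparison. The number that sets the power is therefore the number assessed at 3 months, not the number randomised.

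The paragraph attaches its power claim to 70 and obtains 70 from the participation rate alone. It then expects a tenth of those 70 to be lost. The 80% therefore describes complete follow-up, which the plan itself does not expect. At stake is whether the one power statement in the article is correct as written.

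**Working it through.** **Inputs from the article:** about 100 invited; 70% participation; 70 participants, 35 per arm, allocated 1:1; 10% dropout to the first follow-up; differences of 5.5 and 6.0; 80% power; 5% significance; no imputation.

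**Assumptions, because the article is silent:** two-sided test; the stated 80% holds at exactly 35 per arm; dropout spread evenly over the arms.

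**Step 1. Reproduce the invitation figure.** 70 / 0.70 = 100. This matches exactly, so the figure contains no dropout term.

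**Step 2. Number assessed.** 100 × 0.70 = 70 randomised; 70 × 0.90 = 63 assessed, or 31.5 per arm on average.

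**Step 3. SD implied by the power statement.** With the normal approximation, SD = Δ / [(1.960 + 0.842) × √(2/35)].

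- Anxiety: 5.5 / (2.802 × 0.2390) = 8.21
- Depression: 6.0 / (2.802 × 0.2390) = 8.96

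These SDs are back-solved. The article states none, so 5.5 and 6.0 cannot be reproduced independently.

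**Step 4. Power at 63.** Power = Φ(Δ / [SD × √(2/31.5)] − 1.960). The SD cancels, which leaves Φ(2.802 × √(31.5/35) − 1.960) = Φ(2.658 − 1.960) = Φ(0.698) = 75.7% for both subscales. The relative loss therefore does not depend on the unknown SD.

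| Variant | Power at 5.5 and 6.0 |
|---|---|
| Two-sided, normal approximation, 31.5 per arm | 75.7% |
| Two-sided, noncentral t, 31 and 32 | 75.6% |
| Two-sided, normal approximation, 31 per arm | 75.1% |
| One-sided 5%, normal approximation, 31.5 per arm | 76.2% |

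**Step 5. Difference detectable at 80% power with 63.** It grows by √(35/31.5) = 1.054.

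- Anxiety: 5.5 × 1.054 = 5.80
- Depression: 6.0 × 1.054 = 6.32

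With the t distribution, the standardised difference goes from 0.6794 to 0.7173 (a factor of 1.056), giving 5.81 and 6.33. Both routes round to 5.8 and 6.3.

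**Step 6. For scale only.** Keeping 70 assessed would take 70 / 0.90 = 77.8, so 78 randomised, and 78 / 0.70 = 111.4, so 112 invited.

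**The case against.** The best case for the plan is that this is a pilot, that its 70 is a count of participants and was never promised as a count of completers, and that the loss is small: about 4 points of power, or 0.3 points on a 0 to 21 subscale, for secondary outcomes. Nearly all of that stands. It limits the weight of the point but does not make the power sentence correct.

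Three narrower defences fall short:

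- **The differences may already have been worked out on 63.** The implied SDs would then be 7.79 and 8.50 and the 80% would survive. But the text ties the differences to the sample size it has just given, which is 70.
- **The sample may be enlarged.** The contingency plan allows this only as a possible response to the pandemic; it does not build in the expected 10%.
- **Some dropouts may still be assessed.** The primary outcome section defines dropout by session attendance, so this is possible. The sample-size sentence, however, speaks of dropout up to the first follow-up and goes straight on to losses to follow-up. If some dropouts were assessed, the number would lie between 63 and 70 and the power between about 76% and 80%.

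A reader might infer more than the article supports:

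- **That 35 per arm are not delivered.** They are, as randomised. Whether the pilot convention counts recruited or assessed participants cannot be settled from the article.
- **That expecting little missing data contradicts 10% dropout.** The missing-data sentence credits interviewer training, so it can be read as gaps among those who are assessed. Both statements can be true.
- **That dropouts add no follow-up to the time-to-recovery analysis.** The article says the date a difficulty ceased is asked and recorded. It does not say this happens only at 3 months.
- **That the article hides the lack of a basis for 70 in the primary outcome.** It says openly that no prior effect size or SD was known and offers 70 as a convention.

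**Conclusion.** The point holds, within limits. On the plan's own participation and dropout rates, about 63 of 70 randomised participants are expected to contribute a HADS change score. Power at differences of 5.5 and 6.0 is then about 76% rather than 80%, and 80% power is reached at about 5.8 and 6.3.

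This rests on a two-sided 5% test, on the stated 80% applying at 35 per arm, and on those who drop out having no 3-month HADS score. Sidedness and the choice of approximation move the power only between about 75% and 76%. The finding concerns the accuracy of one power statement on secondary outcomes. It does not undermine the randomised sample size, the feasibility outcomes or the time-to-recovery analysis.

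**What to change.** Restate the sample-size paragraph so that it distinguishes 70 randomised (35 per arm) from about 63 expected to be assessed at 3 months after 10% dropout. Then give the HADS statement at 63, in one of two forms: detectable differences of about 5.8 (anxiety) and 6.3 (depression) at 80% power, or about 76% power at 5.5 and 6.0. The authors should recompute these from the SDs they took from the earlier trial, and state those SDs and the sidedness of the test alongside.

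The cost is a few reworded sentences and slightly less favourable figures. No additional patients, visits or analyses are required.

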### Contingency plan

This study intents to recruit participants within 7 days after the onset of symptoms and start intervention no later than 15 days, which is a considerably short period. This recruitment time frame may be difficult to attain, so additional measures may have to be adopted, namely receive referrals from other hospitals in neighbouring counties (eg, Porto).

Due to the COVID-19, the number of in-person sessions and participants per group may be reduced. However, if necessary, all activities will be home-based. To minimise the potential impact of the pandemic on participation and retention rates, additional mitigation measures may be adopted, including enlarging the recruitment period or an increase in the sample size.

